#### 2.8.2 Assessment of the secondary outcome

Secondary outcome is assessed by the partners at the Jena University Hospital in a longitudinal survey of risk groups.

*2*.*8*.*2*.*1 Data source and sample*. The survey was conducted at three measurement points before, during, and after the implementation of the information campaign, in March—July 2021 (before), March—July 2022 (during) and March—July 2023 (after). All parts of the survey were conducted both in the intervention regions and the remaining German states as the control condition. The evaluation of secondary outcomes is based on the first and third time point, while the second time point served to inform the process evaluation of the campaign (see 2.9.).

A convenience sample of *n* = 740 persons with a minimum age of 18 years was recruited by the market research institute IPSOS. The recruitment was designed to achieve predefined numbers of cases within strata defined by age (<60 years, ≥60 years), education (low, middle, high), specific chronic diseases (e.g., diabetes, chronic diseases, cancer), and regions (intervention vs. control states). Sample recruitment for persons without chronic diseases was realized via an existing consumer survey panel. Sample recruitment for the group of persons with specific diseases, sample recruitment was carried out via self-help groups, general practitioners, social media and by contacting participants of previous studies by IPSOS. After they gave informed consent to participate in the survey study, participants were interviewed online, via telephone or face-to-face, using a standardized questionnaire in German language.

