*2*.*8*.*2*.*2 Sample size considerations*. As the sample size required for the analysis depends on a number of factors (e.g. stability of the outcomes between the survey time points, variance of the outcomes at the survey dates, the intervention effect, which cannot be specified precisely in advance), several scenarios were considered as part of a simulation study. The power simulation was conducted in the statistical software R [26] version 4.0.2) with the R package lme4 [27]. As result a sample size of *N* = 244 for the third survey time point seems to be sufficient for detecting a moderate effect (*d* = 0.5) at a significance level of α = 0.05 with a power of 80%, even with low stability of the outcome variables (correlation of *r* = 0.3 between survey time points). However, the resulting sample size is only sufficient under the assumption that there are no missing values on relevant variables. To allow for a reduction in the effective sample size due to missing values, the sample size estimated from the simulation study was increased by 15%, resulting in a sample size of N = 280.

A necessary condition for the planned analyses and the power simulation carried out is the participation at both, first and third, survey time points. For this reason, the dropout rate must be taken into account for the sample size consideration. Based on the experience from the market research institute a drop-out of about 60% from the first to the third survey time point was used, resulting in a total sample size of *N* = 740 for the first time point.

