*2*.*8*.*2*.*4 Statistical analysis*. To assess the effect of the intervention in the controlled before-after design, a linear mixed model will be calculated with the variables survey time point (first and third time point) and region (intervention and control region). The hypothesis of campaign effectiveness is examined by testing the interaction effect between survey time and region against zero. Survey time point, region and the interaction effect are estimated as fixed effects. Systematic differences between persons are taken into account as random effect. Differences in confounders between the control and intervention regions are adjusted by including the following confounders as covariates in the model: presence of chronic disease, age, gender, education level, health information seeking behavior (frequency of health information seeking and variety of information sources). Since 15% of missing values were already taken into account in the sample size consideration, list wise deletion is used in the analysis to deal with missing values. The analyses will be conducted with statistic software R and the R package “lme4” with a significance level of α = 0.05.

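### The survey analysis justifies listwise deletion by a sample-size allowance and wrongly requires both waves for a mixed model, leaving the baseline data of 60–67% of respondents unused

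*Protocol article*

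**What the plan says.** All statements are in section 2.8.2 of the protocol article.

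- **Missing data (2.8.2.4).** The method and its only stated reason are: "Since 15% of missing values were already taken into account in the sample size consideration, list wise deletion is used in the analysis". The model is a linear mixed model in lme4 with survey time (first and third), region and their interaction as fixed effects, a random person effect, and covariates. The interaction is the test of campaign effectiveness.
- **Who is analysed (2.8.2.2).** "A necessary condition for the planned analyses and the power simulation carried out is the participation at both, first and third, survey time points".
- **Sample size (2.8.2.2).** "As result a sample size of *N* = 244 for the third survey time point seems to be sufficient" for d = 0.5 with 80% power at a correlation of 0.3. Then "the sample size estimated from the simulation study was increased by 15%, resulting in a sample size of N = 280". Finally, "a drop-out of about 60% from the first to the third survey time point was used", which leads to 740 at the first survey.
- **Second survey (2.8.2.1).** The effect evaluation uses the first and third surveys, while "the second time point served to inform the process evaluation of the campaign".

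**The concern.** Two statements are wrong as written. First, enlarging a sample to offset missing values restores the number of usable records. It does not make those records representative, so it cannot justify a missing-data method. The 15% also covers only missing values on relevant variables among participants, not the much larger dropout between surveys.

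Second, a likelihood-based linear mixed model does not need both measurements from each person. Someone seen only at the first survey still informs the baseline mean of their region and, through the between-wave correlation, the estimated change.

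The estimate would then rest on a selected minority of the people interviewed, with some precision lost. Regions are not randomised, the sample is a convenience sample, and the campaign runs in one region only. It could therefore affect who stays in the survey there. If completers in one region start from a higher or lower score, regression to the mean can look like a campaign effect or hide one.

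**Working it through.** **1. The plan's own figures.** 244 × 1.15 = 280.6, which gives the stated 280. 280 / 0.40 = 700, not 740; 740 corresponds to dropout of 1 − 280/740 = 62.2%, which is compatible with about 60%. I do not call 740 wrong. The 244 comes from a simulation whose regional allocation is not given, so it can be neither confirmed nor refuted.

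**2. Share of the 740 left unused.**

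| Basis | Remaining | Unused |
|---|---|---|
| Dropout of 60% only | 740 × 0.40 = 296 | 60% |
| Planned 280 at third survey | 280 | 62.2% |
| 60% dropout, then 15% missing values | 740 × 0.40 × 0.85 = 251.6 | 66% |
| Planned 244 without missing values | 244 | 67.0% |

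**3. Precision.** Assumptions: 1:1 split (not stated in the article), unit variance at both waves, N = 740 at the first survey, m = 252 complete pairs.

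- Complete pairs, variance of mean change per region: 2(1 − r)/126.
- All data: (1 − r²)/126 + (1 − r)²/370.
- At r = 0.3: 1.4/126 = 0.01111 against 0.91/126 + 0.49/370 = 0.00855, a ratio of 0.77.
- In general the ratio is [(1 + r) + (1 − r)m/N]/2.

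| r | Variance ratio | Reduction | Equivalent complete pairs |
|---|---|---|---|
| 0.3 | 0.769 | 23% | 328 |
| 0.5 | 0.835 | 17% | 302 |
| 0.7 | 0.901 | 10% | 280 |

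At r = 0.3 the standard error of the interaction falls from 0.149 to 0.131 SD.

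**4. Bias when dropout depends on the first-wave score.** Illustrative simulation: 370 per region, about one third retained, true interaction 0.50, logistic retention with slopes of 0.5 (intervention) and 0.2 (control) per SD of the first-wave score. The slopes are assumptions. Intervention completers then start 0.18 SD above control completers.

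- r = 0.3: complete pairs give 0.38, or 0.62 with the slopes reversed; the all-data fit gives 0.50 both ways.
- r = 0.7: complete pairs give 0.445, a bias of about 0.055 SD (11%).
- The mechanism is regression to the mean, (1 − r) × 0.18, which is 0.126 at r = 0.3 and 0.054 at r = 0.7, in line with the simulation.
- If the slopes are equal in both regions, neither analysis is biased for the interaction.

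**5. Bias when dropout depends on a stable, unobserved person trait.** Same set-up, with the slopes applied to the person effect instead of the first-wave score.

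| r | Complete pairs | All data (two directions) |
|---|---|---|
| 0.3 | 0.50 | 0.57 / 0.43 |
| 0.5 | 0.50 | 0.56 / 0.43 |
| 0.7 | 0.50 | 0.55 / 0.46 |

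Here the within-person change among completers is unaffected by the selection, while missing-at-random fails for the all-data fit.

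**The case against.** Several defences of the plan are sound.

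- **The listwise sentence alone does not remove the dropouts.** A reader might infer that listwise deletion by itself discards two thirds of the sample. In a long-format lme4 fit, deleting incomplete rows would keep the dropouts' first-wave rows. The exclusion follows from the both-surveys condition in 2.8.2.2, and the two statements must be read together.
- **Planned power is not undermined.** The 740 was chosen so that enough complete pairs remain. What is lost is available efficiency, and the loss shrinks as the correlation rises; r = 0.3 is the plan's deliberately low-stability case.
- **Missing-at-random is not the weaker assumption.** It is tempting to conclude that the all-data fit is simply safer. Step 5 of the working shows otherwise: the two analyses rest on different assumptions, neither contains the other, and the article does not say which dropout mechanism to expect.
- **The size of the bias is assumed.** The article gives no regional dropout pattern, so a statement that the survey effect will be biased has no support.
- **Leaving out the second survey is a stated design choice**, not an error.
- **Attrition sensitivity analyses are often left to a full analysis plan.** Their absence here is therefore not the point.

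What remains is what the article does state: a reason for listwise deletion that does not follow, and a condition that is untrue of the model it names.

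**Conclusion.** The point holds in a limited form. The 15% allowance is not a justification for listwise deletion, and participation at both surveys is not necessary for the stated mixed model. Together these statements leave the first-wave data of about 60–67% of 740 respondents unused.

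The forgone variance reduction of 10–23% rests on a 1:1 split, 252 analysable pairs and correlations of 0.7 to 0.3. The possible bias of about 0.12 SD (r = 0.3) to 0.055 SD (r = 0.7) rests on assumed dropout slopes that differ by region; it shows what could happen and is not a forecast. Because the opposite mechanism biases the all-data fit by a similar order (0.04 to 0.07 SD), the case for change is not that one analysis is right. Using all the data gains precision, and showing both fits can reveal selective attrition that the complete-pair analysis alone cannot.

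Severity is should-fix. Only the secondary survey outcomes are affected; the claims-based primary outcome is not.

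**What to change.** 1. In 2.8.2.4, delete the clause that justifies listwise deletion by the 15% allowance.
2. In 2.8.2.2, limit the both-surveys condition to the power simulation.
3. Fit the stated mixed model to all first-survey participants with all available observations, multiply imputing missing covariates. Keep the third-versus-first-survey by region contrast as the test.
4. Report the complete-pair fit alongside as a sensitivity analysis, and interpret a disagreement between the two as a sign of selective attrition.
5. Adding the second-survey answers to the model is optional.

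The cost is a change of wording and a few lines of code, with no new data. The downside is that the main fit then rests on missing-at-random, an assumption different from, not weaker than, that of the complete-pair analysis. The text should say so.

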### 2.9 Process evaluation—Evaluation of campaign implementation

To ensure replicability and transferability of complex interventions to other contexts, an accompanying process evaluation that assesses feasibility and success of implementation, mechanisms of action, and influencing contextual factors has been recommended [30, 31]. In accordance with this guidance, a prospective process evaluation for the implementation of the SepWiss information campaign was planned, including the elements shown in Fig 3.

**Fig 3 pone.0305107.g003:**
[figure not shown]
SepWiss process evaluation. RPS = risk population survey.

The process evaluation involves all partners of the consortium and serves to 1) support the implementation planning, 2) monitor implementation status and, 3) guide adjustment of implementation strategy, if necessary.

Planned indicators used to inform the process evaluation were e.g., the number of page views on the project website in connection to campaign activities, intermittent analyses of vaccination coverage, results from the three risk group surveys, and results of semi-structured qualitative interviews and quantitative surveys with health professionals actively involved in patient care in Berlin or Brandenburg. These interviews served to identify factors that hinder or facilitate health care professionals’ willingness and ability to increase risk groups’ sepsis knowledge, and to analyze which component of the campaign are used by health care professionals to support their patients’ knowledge.

As an unpredictable force majeure, the at the time ongoing Covid-19 pandemic was taken into account at every step of the process evaluation. Analyses of vaccination coverage from 2021/2022 did not show a negative impact on the uptake of standard vaccinations, but were able to prove positive trends e.g., higher vaccination coverage for pneumococci vaccination in the beginning of 2022 compared to 2019 [32]. Eventually, potential effects of the COVID-19 pandemic on the results of the SepWiss study such as vaccination fatigue post COVID-19 will be discussed in more detail upon publication of the results.

## 3 Results

### 3.1 Current state of the study

The SepWiss information campaign activities started in August 2021. After March 31, 2023, there are no further activities directed at the general public. Educational formats are not actively advertised anymore but are provided upon request. Information materials and recorded formats remain available from the information center. Data collection for assessment of vaccine coverage (primary outcome) and evaluation of the risk group survey (secondary outcomes) have not been finished yet. The evaluation of campaign effects will be ongoing until spring 2024.

## 4 Discussion

SepWiss evaluates the effects of a multi-faceted evidence-based information campaign on vaccination coverage of recommended vaccines as well as sepsis knowledge within the most vulnerable populations in the German federal states of Berlin and Brandenburg. The SepWiss campaign is unique in its scope and design. Previous regional awareness campaigns, like the project "MV vaccinates" (German: “MV impft”) in the German state of Mecklenburg-Vorpommern, did not emphasize the need for evaluating campaign success, and furthermore did not emphasize the element of potentially preventing sepsis by avoiding vaccine-preventable infections. Some of the partners from the SepWiss consortium were involved before in the BMBF-funded project "Vaccination 60+" (German: “Impfen 60+") in the German state of Thuringia, which included an evaluation of an intervention to increase vaccination coverage, but, as a notable difference to SepWiss, did not address the topic of early sepsis detection. Also in international comparison, SepWiss stands out by evaluating the impact of targeted health information on sepsis knowledge as well as vaccination coverage. High-profile nationwide sepsis awareness campaigns have been driven for a long time now by the CDC and the Rory Staunton Foundation in the US, or the UK Sepsis Trust and National Health Service in the UK, respectively. However, none of these are focused on specific risk groups, nor are they closely linked to the issue of vaccine prevention.

The study has important strengths, including its evidence-based design, the multimodal intervention and evaluation strategy, the involvement of public health stakeholders, and the controlled before-after design. However, the evaluation of outcomes, in particular vaccination coverage and attitudes to vaccination, might be influenced by well-known factors such as trust in vaccine efficacy, barriers in access, or risk perception [29], not all of which are specifically addressed and measured in the study. In addition, the effects of the COVID-19 pandemic as an unpredictable force majeure at the time of implementation could not have been addressed in advance by the design of the evaluation of the primary and secondary outcomes. However, the before-after design including control regions still allows to analyze effects in the intervention region. In addition, the planned process evaluation was adapted and carried out in more depth to identify the campaign’s impact mechanisms in the light of the ongoing pandemic. The potential effects of the COVID-19 pandemic at the time of campaign implementation will be discussed along with the reporting of study outcomes.

The SepWiss project helps to better understand which measures are suitable in the German healthcare system to increase vaccination coverage against sepsis-causing infections and to improve the early detection of sepsis. The findings of the project can make a significant contribution to implementing the requirements of the WHO resolution "to include prevention, diagnosis and treatment of sepsis in national health systems strengthening in the community and in health care settings" [2] at the federal level. Taking appropriate measures was also proposed in a unanimous resolution of the 2018 German Conference of Health Ministers [33]. The multimodal SepWiss campaign addresses the insufficient vaccine uptake among people with underlying diseases and among the elderly in Germany [25] by trying to increase sepsis knowledge among the risk population, which has been shown to positively influence vaccine hesitancy [10], as well as train health care workers, which potentially leads to improved vaccine uptake [11]. With this, the study contributes to protecting the population from vaccine-preventable diseases. It also supports the recommendations from the European Council to aim for an influenza vaccination coverage of 75% among people > 60 years of age [34], which is also part of the German national vaccination strategy [35]. Evaluating the campaigns effects in the metropolitan region of Berlin as well as in the more rural state of Brandenburg, results are expected to be particularly valuable in informing nationwide sepsis awareness activities in the future.

## Abbreviations

GP: general practitioner
LOI: Letter of Intent
MHB: Brandenburg Medical School (German: Medizinische Hochschule Brandenburg)
RPS: risk population survey
STIKO: Standing Committee on Vaccination (German: Ständige Impfkommission)
ToC: Theory of Change
